### The role of maternal posture

In the 1800s, it was noted that women would give birth in upright positions using posts, hammocks or furniture, or that women might kneel, crouch, or squat using bricks, stones, or a birthing stool [31]. Upright positions adopted during the first stage of labour have been shown in a systematic review to reduce the duration of labour by about one hour [32]. Upright postures may enhance progress in the second stage of labour and reduce operative delivery, however the limited evidence available is inconclusive. A systematic review of maternal position in the second stage of labour revealed several benefits due to upright posture (e.g. fewer instrumental deliveries, fewer abnormal fetal heart rate patterns, a trend to shorter second stage) however, it also revealed a possible association with more blood loss [33]. In this review, it was suggested that blood loss may have been more accurately estimated in the women allocated to upright birth in a specially designed birth chair in which blood loss was collected in a receptacle. Assuming an upright kneeling or squatting position for the second stage of labour may facilitate vaginal delivery, by enabling the mother to bear down more efficiently with the alignment of physiological and gravitational forces, as well as tilting the pelvis to a more favourable (less oblique) orientation to the direction of the uterine and bearing down forces. However, in practice the second stage of labour is often performed in recumbent or semi-recumbent positions, which some claim enables birth attendants to better monitor and gain access to the baby [31].

### Pilot study

We conducted a pilot study in the form of a RCT, to determine the feasibility of a larger RCT to evaluate this new method of gentle fundal pressure called “gentle assisted pushing” (GAP), which was performed with the woman in an upright posture. The pilot study protocol was approved by the Ethics Committee, East London Hospital Complex, and the Committee for Research on Human Subjects, University of the Witwatersrand.

This two-armed RCT recruited 120 healthy, nulliparous women with a singleton pregnancy in cephalic presentation at ≥35 weeks who consented to participate. Women undelivered by 15 min of bearing down (second stage) were randomized (1:1) to 1) gentle assisted pushing in an upright posture, or 2) upright posture only. The attendants were two research midwives who were taught the fundal pressure technique by the lead investigator. During contractions, steady firm fundal pressure was applied using the palms of both hands in the direction of the pelvis using only the strength of her forearms. Steady, sustained pressure was maintained for the full duration of each contraction or 30 s, whichever was shorter. Forceful or rapid pressure and the use of body weight to apply pressure were avoided. The results of this unpublished pilot study showed a non-significant trend towards reduce rate of operative delivery. From this pilot, it was concluded that the GAP method was clinically feasible and that the results justified a larger trial to study the effectiveness and safety of this intervention, and its relationship to posture, in the second stage of labour.

This larger trial will add to the body of knowledge on upright posture versus recumbent posture. By additionally using gentle assisted pressure combined with the upright posture, the expulsive forces acting on the uterus should be optimised. To differentiate possible effects of gentle assisted pushing and posture, and to supplement the evidence base on the effectiveness of upright posture, a three-armed comparison will be used.

### Study objectives

This three-arm trial aims to evaluate the use of gentle assisted pushing in an upright posture (GAP). We will determine whether:GAP is associated with reduced duration of second stage of labour, and improved neonatal and maternal outcomes, compared with current routine practice (typically recumbent/supine posture).Upright posture alone is associated with a reduced duration of second stage of labour, and improved neonatal and maternal outcomes, compared with current routine practice (typically recumbent/supine posture).GAP (gentle fundal pressure in an upright posture) is associated with reduced duration of second stage of labour, and improved neonatal and maternal outcomes, compared with upright posture alone.

## Methods

### Study design

The GAP study is a multicentre, randomized, controlled, unblinded, clinical trial with three parallel arms (1:1:1). Please see Fig. 1 for a graphical outline of the study.

**Fig. 1 Fig1:**
[figure not shown]
Flow chart for the GAP study

### Study setting

The study will be conducted in four sites at three maternity facilities in South Africa, namely:Frere Hospital, East London – a tertiary-level hospital with approximately 800 beds in total, with an estimated 570 deliveries per month. There are two study sites at Frere Hospital:oDancan Village Day Hospital - Midwife-led obstetric unitoFrere labour ward - Obstetrician-led obstetric unitCecilia Makiwane Hospital, East London – a secondary-level hospital with approximately 700 beds in total, with an estimated 400 deliveries per monthButterworth Hospital – a district hospital with approximately 400 beds in total, with an estimated 400 deliveries per month

### Study participants

All women attending participating hospitals for delivery (who meet the inclusion criteria) during the study period will be approached for participation in this study.

The eligibility criteria are:Equal to or greater than 18 years old;Nulliparous women;Gestational age ≥ 35 weeks;Singleton pregnancy;Vaginal delivery anticipated;Cephalic fetal presentation;Baby’s heartbeat detected;No chronic medical conditions, including heart disease, epilepsy, hypertension, diabetes mellitus and renal disease;No obstetric complications, including hypertensive disorders of pregnancy, cephalo-pelvic disproportion, antepartum haemorrhage, intra-uterine growth restriction, fetal distress, intra-amniotic infection; andWilling and able to provide consent

Women whose labours are induced or augmented, or women with HIV, are not excluded from this trial. However, this information will be captured in the trial forms.

### Recruitment and screening procedures

In participating facilities, nulliparous women ≥18 years old will be approached with information about the trial. Women who are in latent phase of labour and who meet the eligibility criteria will be fully counselled and informed about the trial. The following guidelines will be used for screening:The woman should be sufficiently comfortable to make an informed choice.Information should be provided in her home language.She will be given an information sheet and offered time to reflect and ask questions, or to consult with family members.If she agrees, she will sign the informed consent formIlliterate participants will have the consent form read to them.Verbal consent will be witnessed by an independent signatory.Following receipt of the signed consent form, baseline demographic and clinical data will be recorded on the screening form.Screened women will be given a screening number, including women who decline to take part and those who are not eligible. All screening forms will be kept by the study team.

### Sampling and allocation

Recruited women who reach second stage of labour without major complications will be randomized. The randomization sequence will be generated by the WHO/RHR Statistics and Informatics (SIS) team. This will be computer-generated in balanced blocks of variable size, in a ratio of 1:1:1 for the three study arms. Details of the group allocation will be concealed on cards inside a sequentially-numbered series of sealed, opaque envelopes. These will be prepared by the SIS team, separately for each study site. Allocation will be performed by the research assistant, by opening the next numbered envelope in the series. The assignment schedule will be stored at WHO, and will not be accessible to the on-site research teams.

### Study interventions

Participants will be allocated to one of the following intervention groups:Arm 1: GAP (gentle fundal pressure in an upright posture)Arm 2: Upright posture onlyArm 3: Routine practice (typically recumbent/supine posture)

Labour ward staff at the study sites will be trained in these study procedures before the start of recruitment.

#### Arm 1: GAP (gentle fundal pressure in an upright posture)

The principle of the procedure is for the birth attendant (a midwife or doctor) to apply steady (firm yet gentle) manual pressure on the uterine fundus in the direction of the pelvis, for the full duration of each uterine contraction, but not exceeding 30 s. Forceful or rapid pressure is to be avoided.

Gentle assisted pressure will be applied by attendants who have been trained in the procedure, via a video teaching aid and practical demonstration by the study team. These training materials and methods will be standardized to ensure comparability of training and GAP administration across study sites. The woman will be assisted to assume an upright kneeling or squatting posture on the bed. The trained birth attendant will kneel behind her on the bed or stand behind her with the woman positioned at right angles to the length of the bed and back close to the side of the bed. The trained birth attendant will wrap her arms around the woman passing below her axillae, and place both open palms, overlapping, on the fundus of her uterus. Steady pressure in the long axis of the uterus will be applied only during contractions. The duration of pressure will be limited to 30 s, with a minimum of 30 s rest before the next pressure.

The position of the trained birth attendant in relation to the mother ensures that excessive force using the assistant’s weight cannot be used, as occurs with conventional fundal pressure when the woman is supine and the trained birth attendant is standing alongside her. The upright posture is integral to this intervention. During training, a manikin will be used with a small air-filled bladder between the trained birth attendant’s hands and the manikin abdomen, connected to a beaumanometer so that the amount of pressure can be monitored.

#### Arm 2: Upright posture

Participating women will be encouraged to assume an upright crouching or kneeling position during the second stage of labour. When the baby’s head is ‘crowning’, the trained birth attendant may choose to move the woman to a recumbent position for the birth.

#### Arm 3: Routine practice (recumbent/supine posture only)

The current posture as practiced in the participating sites will be used.

In all intervention arms, the trained birth attendant encourages the women to bear down. All other delivery procedures, such as fetal heart monitoring and routine oxytocin after the birth, are performed according to the usual hospital routine and will not differ between the groups.

For Arm 3 (routine practice), if the woman remains undelivered 30 min after randomization, fundal pressure or changes in posture may be considered necessary by the birth attendant according to routine local practice. Additional procedures or treatments performed at the discretion of the attendant will then be recorded in the study form.

At any stage of the labour, routine procedures such as change in posture, oxytocin administration, forceps or vacuum delivery or caesarean section will be available as considered indicated by the responsible clinician. If forceps, vacuum delivery or caesarean section is required, GAP and/or upright only posture will be stopped.

Electronic fetal heart rate monitoring is not routinely used in the study institutions in uncomplicated pregnancies; therefore, this equipment is unlikely to interfere with the administration of the interventions in this study. Auscultation of the fetal heart rate will be performed after each contraction following randomization. If electronic monitoring is considered necessary by the birth attendant, the GAP procedure will not interfere with monitoring as the monitor is positioned on the anterior aspect of the uterus while pressure is applied to the fundal aspect.

### Study outcomes

The primary outcome is defined as mean time (minutes) from randomization to delivery.

Secondary outcomes include the following:Delivery outcomes:oNo spontaneous delivery within 15 min of randomization;oOperative delivery (vacuum, forceps or caesarean section); andoEpisiotomy or 2nd/3rd degree tears.Neonatal outcomes: oCord blood pH < 7.2;o5-min Apgar score <7;oNeonatal injury;oNeonatal encephalopathy;oAdmission to neonatal high care nursery for ≥24 h; andoNeonatal death.

Mothers will also be asked to grade their discomfort experienced during the second stage of labour. All adverse events and serious adverse events will also be recorded.

### Safety considerations

No drugs are being tested in this study. We are testing interventions that are not taught or sanctioned by teaching institutions in South Africa or elsewhere due to lack of evidence, but practiced to varying degrees of frequency. WHO does not currently recommend this procedure. The GAP method of applying fundal pressure has been specifically developed to avoid the commonly used, more vigorous form of fundal pressure. Therefore, interventions which are practiced to some extent (fundal pressure and posture) but for which there is little supporting evidence are being tested by the study. We do not anticipate any specific safety concerns over and above those usually anticipated in the second stage of labour.

However, some women may find specific birth positions and/or gentle fundal pressure uncomfortable. The research staff will assist and support women to use the allocated study position. Women may benefit from the additional support. However, should a woman choose to change birth position, or withdraw from the study for any reason, it will not affect the medical care to which she is entitled.

### Adverse events

An adverse event is any untoward medical occurrence in a patient or clinical investigation subject and which does not necessarily have a causal relationship with this treatment. An adverse event can therefore be any unfavourable and unintended sign (including an abnormal laboratory finding), symptom, or disease temporally associated with the use of a medicinal (investigational) product, whether or not related to the medicinal (investigational) product.

Any adverse event that requires treatment will be reported an Adverse Event (AE) form and the principal investigator immediately alerted.

The serious adverse event form will be completed in the following circumstances:The woman has been transferred to another department or hospital in relation to an adverse event after enrolment in the trial.An adverse event has caused prolonged hospital stay.The woman has been re-admitted to the hospital for further care of an adverse event that has occurred while she was in the trial.The adverse event has caused permanent loss of function of a system or organ.The adverse event is considered to be life threatening.The adverse event has resulted in death.

Reporting of AEs and SAEs will be done using an adverse event (AE) form and serious adverse event (SAE) form. These forms will be completed by data collectors and the principal investigator informed as soon as possible. The WHO project manager will be notified of the AE or SAE within 24 h, and the DSMC will be notified of SAEs within 24 h (accelerated reporting).

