### Potential benefits and risks of fundal pressure

In well-resourced settings, a prolonged second stage of labour is usually overcome by assisted vaginal delivery or caesarean section. In lower-income countries, for the majority of births, instrumental or operative delivery methods may not be available; and timely transfer to a service with these facilities may not be feasible. In these settings, fundal pressure may be an effective way of expediting the birth of a baby, and potentially reducing the risk of neonatal morbidity and mortality associated with a prolonged and difficult birth. In addition, this intervention may be valuable for women in whom instrumental delivery is contraindicated (such as HIV infection) and for whom assistance in the second stage of labour is necessary. However, even in settings where instrumental or operative delivery is available, fundal pressure may reduce the need for their use and, thereby, reduce the risk of associated third-degree tears or surgery. The potential benefits, therefore, have implications for obstetric care at all levels.

Fundal pressure manoeuvres of variable force and direction are commonly used by birth attendants with potentially harmful effects. Maternal complications ascribed to these ‘conventional’ fundal pressure manoeuvres include perineal tears, uterine rupture, uterine inversion, pain, hypotension, respiratory distress, abdominal bruising, fractured ribs, and liver rupture [19–26]. Excessive fundal pressure has also been cited as a predisposing factor for amniotic fluid embolism [27]. In the neonate, fundal pressure has been implicated as a possible cause of fractures and brain damage [28, 29]. The theoretical basis for the latter is that applying mechanical forces to the uterus to increase intrauterine pressure could cause a concomitant increase in fetal intracranial pressure. This, in turn, could lead to a decrease in fetal cerebral blood flow and subsequent cerebral handicap in the infant. The same mechanism has been postulated to occur in cases of cerebral palsy following uterine tetany or forceps delivery. In addition, if used in the presence of cephalo-pelvic disproportion, the risk of maternal and neonatal injury would be high.

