### Data entry

The data will be entered in OpenClinica™, a web-based, fully GCP-compliant data management system. The data analyst at WHO Geneva will develop the data management system, provide hosting, data back-ups and maintenance of the system.

A validation system will be built into the data management system to ensure consistency, accuracy and completeness of the data collected (range checks, consistency checks and skips). Double data entry will be performed and queries will be resolved as much as possible before discharge of the woman from hospital. First and second data entry will be done as soon as the case report forms are completed.

It is unlikely that serious side-effects of the intervention will occur. Adverse events and serious adverse events, whether thought to be related to the trial intervention or not, will be recorded by the researchers on the adverse events CRFs which will be submitted to the DSMC and the relevant ethics committees.

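### The rule for starting an adverse event form depends on need for treatment, which conflicts with the protocol's recording of all adverse events, and two serious-event triggers cover only the mother

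*Protocol article*

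**What the plan says.** The Adverse events section of the protocol article opens with a broad definition: "An adverse event is any untoward medical occurrence in a patient or clinical investigation subject". It attaches no severity or treatment threshold. The section then gives a reporting rule: "Any adverse event that requires treatment will be reported an Adverse Event (AE) form and the principal investigator immediately alerted". Its last paragraph adds: "Reporting of AEs and SAEs will be done using an adverse event (AE) form and serious adverse event (SAE) form".

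Other sections are unconditional. Study outcomes states: "All adverse events and serious adverse events will also be recorded". Data entry states: "Adverse events and serious adverse events, whether thought to be related to the trial intervention or not, will be recorded by the researchers", and puts them on the adverse event case report forms that go to the data safety and monitoring committee (DSMC). Criteria for discontinuation of the study promises the DSMC all adverse events on an expedited basis.

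The Background section on potential benefits and risks lists the maternal complications ascribed to conventional fundal pressure: "perineal tears, uterine rupture, uterine inversion, pain, hypotension, respiratory distress, abdominal bruising, fractured ribs, and liver rupture".

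The serious adverse event (SAE) form has six triggers. The first reads: "The woman has been transferred to another department or hospital in relation to an adverse event after enrolment in the trial". The readmission trigger is also worded for the woman. The other four (prolonged stay, permanent loss of function, threat to life, death) name no particular person. The DSMC is to hear of SAEs within 24 hours. Follow-up procedures has both women and neonates followed until discharge.

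**The concern.** The treatment sentence is the one place where the article says which events start an adverse event form. It attaches both the form and the alert to need for treatment. The other sections assume a complete record but do not say how an untreated event enters it, and no other form is named.

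This matters because of how the result will be used. The Discussion says that a beneficial GAP method can be promoted in place of uncontrolled fundal pressure, and the Background says that the safety of fundal pressure has not been established. The harm data therefore need to be complete, and gathered by the same rule at all four sites and in all three arms. The trial is unblinded, so a threshold that depends on a judgement about treatment is less secure than one that takes in every event.

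The SAE wording raises a smaller, separate question. The Background names fractures and brain damage as possible neonatal harms, yet moving a baby to another department or hospital because of an adverse event does not meet the transfer trigger.

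**Working it through.** No arithmetic applies: the article gives no adverse event rates and no proportion of events needing treatment. The check is a comparison of the passages.

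**Which adverse events are covered?**

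| Section | Scope | Treatment condition? |
|---|---|---|
| Adverse events, definition | Any untoward occurrence | No |
| Adverse events, form and alert sentence | Events needing treatment | Yes |
| Adverse events, last paragraph | Adverse events and SAEs, on their forms | No |
| Study outcomes | All | No |
| Data entry | All, related or not | No |
| Criteria for discontinuation of the study | All, sent to the DSMC | No |

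One statement of six carries the condition. If it governs the form, the record cannot be complete as the other sections say. If it governs only the alert, it is misworded, because it names the form as well.

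**Which listed maternal harms depend on the answer?**

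- Perineal tears: second- and third-degree tears are a secondary outcome, so these do not depend on the form.
- Pain: at least partly captured, because mothers grade their second-stage discomfort.
- Uterine rupture, uterine inversion, liver rupture: these would ordinarily need treatment, so they meet even the narrow rule.
- Abdominal bruising, hypotension, respiratory distress, rib injury: not listed outcomes. The milder, untreated cases could be left off the form under the literal reading.

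**Which neonatal events depend on the SAE triggers?**

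1. Two of the six triggers (transfer, readmission) are limited to the woman; four are not.
2. A baby transferred because of an adverse event becomes an SAE only if one of those four also applies.
3. If none does, the 24-hour notice to the DSMC for SAEs is not triggered.
4. Readmission comes after the follow-up that the article describes, for mother and baby alike, so transfer is the more consequential of the two.

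**The case against.** The strongest reply is that the treatment sentence is an escalation rule. It does not contain the word only, and it ends with the alert to the principal investigator. The last paragraph of the same section and the Data entry section both put adverse events on the form without condition: they "will be recorded by the researchers on the adverse events CRFs which will be submitted to the DSMC". This reading is plausible and may well be what was intended. It does not remove the conflict, because the sentence as written makes need for treatment the criterion for the form too. The last paragraph says which form to use, not which events qualify.

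Several stronger readings are tempting, and the documents do not support them.

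- A reader might infer that the protocol expects these harms and will miss most of them. The Background ascribes them to conventional manoeuvres. Safety considerations says GAP was developed to avoid the vigorous form, and anticipates no specific concerns beyond those usual in the second stage, apart from possible discomfort. Nothing shows what share would be missed.
- A reader might infer that the birth attendant decides in each arm what gets counted. The article says the forms are completed by data collectors, or by the researchers.
- A reader might infer that no structured check for these harms exists. The case report forms are available on request but not shown, and a manual of operations is mentioned, so this cannot be asserted.
- A reader might infer that injured babies are lost to the comparison. Neonatal injury, encephalopathy, high-care admission of at least 24 hours and death are secondary outcomes in every arm, and the article elsewhere sends all adverse events to the DSMC. What is affected is classification as an SAE and the 24-hour notice.

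**Conclusion.** The point holds as an internal conflict with a limited consequence. The sentence that ties the adverse event form to need for treatment cannot stand beside the definition in its own section and the all-event statements elsewhere. Followed literally, it could leave untreated bruising, hypotension, or minor rib or chest injury off the form, so maternal harms may be under-ascertained. This rests on the assumption that some staff would read the sentence literally. The extent cannot be estimated from the documents, and the article does not establish that harms would go largely uncounted or that the counts would differ between arms. The two SAE triggers limited to the woman are a smaller, separate gap, softened by the other four triggers and by the neonatal secondary outcomes. Neither issue affects the primary outcome. Both should be corrected, because the trial is meant to inform whether GAP is promoted.

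**What to change.** In the Adverse events section, state that the adverse event form is completed for any adverse event, treated or not, and that need for treatment decides only whether the principal investigator is alerted immediately. That brings the section into line with Study outcomes, Data entry and Criteria for discontinuation of the study. In the SAE list, extend the transfer and readmission triggers to the woman or her baby.

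The change is one sentence and two short wording edits, with matching edits to the form instructions if they repeat the current rule. The downside is more minor events to enter and somewhat more SAE reports. No new checklist is asked for here, since the existing case report forms may already contain one.
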